### Study design

This prospective intervention study uses a pre–post design (figure 1). Control patients will be enrolled first (control period), followed by a training phase during which HCPs in the study wards will be trained to implement the intervention. Once the HCPs have undergone training sessions, the intervention period will start. Enrolment during both the control and intervention period will stop once the target sample size is reached, with patient follow-up continuing for 4 months post-discharge. Based on the pilot study, the control and intervention periods are each expected to last approximately 6 months, and the training phase will last around 2 months. Figure 1 provides a schematic overview of the study design. Study enrolment began in September 2024, and recruitment of participants for the intervention group is currently ongoing as of April 2025.

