Box 1The inclusion and exclusion criteria in the study. Patients meeting exclusion criteria 1–9 are excluded at the time of hospital admission, while those meeting exclusion criteria 10–15 are excluded at the time of dischargeInclusion criteria65 years or older. Manages their own medications, either independently or with support from an informal caregiver, prior to inclusion.Exclusion criteriaChecked at hospital admissionRegistered in a region outside the study hospital (limited data availability).Admitted from a nursing home (no own medication management prior to admission).Unable to receive information or provide consent independently (due to cognitive impairment or unresponsiveness).Already included in the study.Patient delocalised to the study ward with another medical discipline responsible for the patient’s care (formally, no study ward patient).In a late palliative phase prior to inclusion (intervention not suitable).Unable to communicate in Swedish (hindering intervention delivery).Has restricted personal information in the EHR (limited data availability).Admitted for transplantation (intervention not suitable).Checked at hospital dischargeDischarged to a nursing home (intervention not suitable).Patient transitions to late palliative phase during the hospitalisation (intervention not suitable).The patient is transferred to a non-study ward and is discharged from there (hindering intervention delivery).The patient dies during the course of the hospital stay (hindering intervention delivery).No medication changes that last post-discharge during the hospitalisation (intervention not suitable).The duration of stay on the study ward is less than 48 working hours (excluding time from 16:00 before weekends/public holiday to 08:00 the day after a weekend/public holiday) (hindering intervention delivery).EHR, electronic health records.

The researchers, who are employed by the hospital, screen the admission lists of the study wards daily on weekdays to identify eligible patients, who are then asked for inclusion by the researchers or clinical pharmacists on the ward. Eligibility is primarily determined through the patient’s electronic health records (EHR), with any uncertainties resolved through discussions with HCPs at the study wards. Once identified, patients are informed both verbally and in writing, and written informed consent (online supplemental material I) is requested. Patients meeting exclusion criteria 10–15 in box 1 are excluded at discharge.

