During the recruitment of control patients, all patients fulfilling the inclusion and exclusion criteria are invited to participate. During the intervention period, patient inclusion is determined based on the capacity of the pharmacists performing the intervention. The pharmacists’ capacity will be evaluated through regular feedback discussions, ensuring that the inclusion process aligns with their workload. If the number of eligible patients exceeds the pharmacists’ capacity, the pharmacist, in collaboration with the research team, will determine how many eligible patients can be included. To prioritise which patients to include, a random priority number will be generated for each eligible patient at the study ward level using Microsoft Excel, with those assigned the highest priority included first.

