#### Secondary outcomes

The proportion of patients with complete medication-related discharge documentation. This will be assessed using the CMDD-M to determine the prevalence of patients achieving the maximum score of 9 points.Improvement in patients’ perceptions of knowledge and involvement in discharge medication communication, and their sense of security in post-discharge medication management. This will be assessed by the average score by the Patient Involvement in Medication Communication at Hospital discharge Questionnaire (PIMCH-Q) (online supplemental material IV). It consists of eight statements rated on a 4-point Likert scale. It is designed with three dimensions: perception of knowledge, involvement and sense of security and aims to measure patients’ perceived involvement in medication communication during hospitalisation and their sense of security in managing medications after discharge. The questionnaire will be sent to patients 1-week post-discharge.Adherence to medication changes made during hospitalisation that persist post-discharge. This will be assessed by measuring the number of instances of non-adherence. Non-adherence to a medication change is defined as follows:New or modified medications: a medication initiated or modified during hospitalisation (ie, changes in strength, dose or formulation) that is not dispensed from a community pharmacy within 14 days post-discharge. This applies regardless of whether the reason is a missing prescription or the patient not filling the prescription. Changes in strength or dose are included only when they create a safety risk for the patient if the previous prescription is used (eg, reducing the dose of a tablet from 10 mg once daily to 2.5 mg once daily, which would require the patient to split the same tablet two times to get the correct dose, a practice considered unsafe).Discontinued medications: a medication discontinued during hospitalisation (or with altered strength or formulation), that is, erroneously dispensed using a previous prescription within 120 days post-discharge.The rationale for collecting data up to 120 days post-discharge is based on standard pharmacy practices in Sweden, where medications are typically dispensed for a 90-day (3-month) supply at a time. Patients may have leftover supplies of discontinued medications at home and continue using them. However, if these medications are not refilled at a pharmacy within 120 days, the patient is considered adherent to the discontinuation.The proportion of patients who are fully adherent to the medication changes made during hospitalisation that persist post-discharge. This will be assessed by determining the prevalence of patients who have no instances of non-adherence as described above.Unplanned healthcare visits post-discharge. This will be assessed using the following outcome measures:The prevalence of patients with at least one unplanned hospital revisit (a composite measure of unplanned readmissions and emergency department visits) at 7, 30 and 90 days post-discharge.The prevalence of patients with at least one unplanned readmission at 7, 30 and 90 days post-discharge.The prevalence of patients with at least one emergency department visit (not followed by admission) at 7, 30 and 90 days post-discharge.The time to the first unplanned hospital revisit within 90 days.The time to the first unplanned readmission within 90 days.The time to the first emergency department visit within 90 days.The prevalence of patients with at least one potentially medication-related hospital readmission at 7, 30 and 90 days post-discharge, assessed using the validated Assessment Tool to identify Hospital Admissions Related to Medications (AT-HARM10).^49 50^

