#### Demographic data

Demographic data collected from the EHR will include age, gender, renal function, admission and discharge dates, medication treatment at admission and discharge, whether the patient has support by automatic dose-dispensation of medications, disease diagnoses, primary diagnosis for admission, home care support, whether the patient lives alone and the number of emergency department visits and hospital admissions in the past year. Information about patients’ education level will be gathered through the researchers asking the patients at inclusion.

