### Statistical analysis

A full statistical analysis plan will be finalised prior to any analyses. Statisticians from the Uppsala Clinical Research Center will oversee the statistical analyses. The primary analysis will follow the ITT principle, including all included patients in their assigned groups, regardless of protocol adherence. Additional analyses will include per-protocol analyses, that is, excluding patients with protocol violations.

Descriptive analyses of the study population will be performed, with continuous data presented as mean±SD for normally distributed variables or as median and range for non-normally distributed variables. Categorical variables will be reported as frequencies and percentages. All outcomes will be summarised by study group, overall and by ward, descriptively. Comparative statistics between study groups will be conducted, with all statistical tests being two-sided and a p value<0.05 considered statistically significant.

Models for analysing primary and secondary outcomes will include both unadjusted and fully adjusted analyses. Adjustments will account for age, gender, education level, ward type (geriatric or surgical), number of medication changes persisting post-discharge, number of medications at discharge, support by automatic dose-dispensation of medications and duration of hospitalisation. Effect estimates, including ORs, HRs and rate ratios will be presented with 95% CI and p values.

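### With control and intervention groups recruited in sequence on the same wards, the one-inclusion rule tends to under-represent repeat attenders in the intervention group, and the adjustment list omits prior attendance

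*Protocol article*

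**What the plan says.** - **The rule.** Box 1, under Study population and recruitment, lists "Already included in the study" fourth among the exclusions checked at admission. It carries no period qualifier, so it applies within each period and across the two.
- **Order and timing.** Study design states: "Control patients will be enrolled first (control period), followed by a training phase". It adds that "the control and intervention periods are each expected to last approximately 6 months, and the training phase will last around 2 months".
- **Sampling.** In the control period "all patients fulfilling the inclusion and exclusion criteria are invited to participate". In the intervention period numbers may be capped by pharmacist capacity, in which case "a random priority number will be generated for each eligible patient at the study ward level using Microsoft Excel". That draw is made among eligible patients, so it cannot bring back anyone the rule has already excluded.
- **Outcomes.** Secondary outcomes include "The prevalence of patients with at least one unplanned hospital revisit" at 7, 30 and 90 days, the matching readmission and emergency-visit outcomes, and times to first event within 90 days.
- **Covariates.** Demographic data includes "the number of emergency department visits and hospital admissions in the past year". The adjustment list in Statistical analysis has age, gender, education, ward type, "number of medication changes persisting post-discharge, number of medications at discharge, support by automatic dose-dispensation of medications and duration of hospitalisation". Prior attendance is not in it.
- **Interrupted time series.** Its outcome list (Exploratory analyses) covers documentation, questionnaire and adherence outcomes, and no revisit or readmission outcome.

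**The concern.** The rule reads as neutral but does not act equally on the two groups. A repeat attender in the control period still contributes one index stay to the control group. A control participant who comes back in the intervention period contributes nothing to the intervention group.

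The removal is also tied to the outcome, because people are barred on account of having been readmitted to a study ward. Training lasts about 2 months and revisits are counted to 90 days. A control discharged at the end of the control period and readmitted unplanned to a study ward between about day 61 and day 90 is therefore a control event, and that same stay cannot become an intervention inclusion.

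At stake is the reading of the secondary utilisation results. Any lean would have a predictable direction, in favour of the intervention. The unadjusted models would carry it, and the adjusted models lack the collected variable best placed to reduce it.

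**Working it through.** **Inputs from the protocol.** 115 patients per group; periods of about 6, 2 and 6 months; same wards. The protocol gives no revisit rate, no share of patients who return and no count of exclusions under this rule, so there is no planned figure to reproduce. All rates below are assumptions.

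**1. Mixture calculation.** Let r be the share of the eligible pool that attends in both periods and p the fraction of those enrolled as controls. The repeater share is r in the control group and r(1 − p)/(1 − rp) in the intervention group. Take p = 0.6 and no intervention effect.

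With a 90-day revisit risk of 0.50 in repeaters and 0.25 in others:

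| r | Intervention share | Control risk | Intervention risk | Gap (points) | Null OR |
|---|---|---|---|---|---|
| 0.05 | 0.02/0.97 = 0.021 | 0.2625 | 0.2552 | 0.7 | 0.96 |
| 0.15 | 0.06/0.91 = 0.066 | 0.2875 | 0.2665 | 2.1 | 0.90 |
| 0.20 | 0.08/0.88 = 0.091 | 0.3000 | 0.2727 | 2.7 | 0.875 |

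With milder risks (0.45 and 0.30), the null OR runs from 0.98 at r = 0.05 to 0.93 at r = 0.20.

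**2. Removal calculation.** Suppose the would-be intervention pool has risk 0.35, and a share s with risk q is removed. The remaining risk is (0.35 − s·q)/(1 − s).

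- s = 0.02, q = 0.45: 0.348, a shift of −0.2 points (OR 0.99).
- s = 0.05, q = 0.55: 0.339, −1.1 points (OR 0.95).
- s = 0.10, q = 0.55: 0.328, −2.2 points (OR 0.91).
- s = 0.15, q = 0.65: 0.297, −5.3 points (OR 0.78). This is an extreme case.

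**3. Simulation with no effect.** Each person had a gamma-distributed frailty driving both study-ward admission and revisit risk. The 48 scenarios crossed control risk (0.25 or 0.40), frailty variance (0.5, 1 or 2), mean admissions per 6 months (0.02 to 0.2) and capture (0.3 or 0.6). If each person could enter once per period, the two groups' risks agreed within noise of about 0.3 points. Under the rule as written, 40 of the 48 scenarios gave an intervention risk within about 2 points of control. Two exceeded 3 points (3.6 at control risk 0.25 and 5.0 at 0.40), both with about 25% of would-be intervention patients removed.

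**4. Against the precision available.** The standard error of a risk difference at risk 0.35 is √(2 × 0.35 × 0.65/115) = 0.063, or 6.3 points. The difference detectable with 80% power from 0.35 is about 16 points. A spurious gap of 0.35 v 0.31 would reach p < 0.05 only about 9% of the time.

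**5. How long a look-back must be.** With even enrolment over months 0–6 (control) and 8–14 (intervention), the gap between a control date and an intervention date runs from 2 to 14 months and is symmetric about 8. About half of the gaps exceed 8 months, so a window equal to control plus training time (6 + 2 = 8) would leave much of the asymmetry in place. A 14-month window covers all of them.

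**The case against.** **The rule is legitimate.** It avoids non-independent records and carry-over from one period to the other. This stands, and nothing here argues for dropping it.

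**A reader might infer that the rule strips repeat attenders from the intervention group only.** The text does not support that. The rule also bars second inclusions within each period. Repeat attenders who declined, were missed, or were last admitted before the study can still enter the intervention group. The accurate statement is under-representation.

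**The control pool may have been depleted too.** Intervention development reports pilot studies with 106 patients on geriatric and surgical wards of the same hospital, ending in May 2024, about four months before enrolment opened. The protocol does not say whether those participants count as already included, or whether the wards were the same. If they count, part of the asymmetry is offset. This stands as an open question.

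**The size is assumed and small.** This stands. A barred patient must return to one of three wards in the intervention window and otherwise qualify, which makes the larger removal shares doubtful.

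**The consequence is limited.** This also stands. The utilisation outcomes are secondary, the protocol itself says that powering for revisits was not feasible, and it concedes that a non-randomised pre–post design limits causal claims. That general caveat does not name this mechanism or its direction.

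**It belongs in the statistical analysis plan.** This holds only in part. A sensitivity analysis and an exclusion count could properly be left there. The covariate list, however, is stated in the article as the full adjustment, and it leaves out a collected variable that bears directly on these outcomes.

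**Conclusion.** The point holds in a limited form. Sequential recruitment on the same wards, combined with a rule that has no period limit, tends to leave fewer repeat attenders in the intervention group. If those who return have a higher revisit risk, the revisit, readmission and emergency-visit odds ratios and hazard ratios are expected to lean toward the intervention with no true effect.

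Under assumed inputs the lean is about 0 to 3 percentage points in 90-day revisit risk, and about 5 points only in extreme scenarios. Both are below one standard error at 115 per group. The calculations are for risks and odds ratios; the hazard ratios should lean the same way but were not computed.

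A reader might go further and say that these outcomes are biased as a matter of fact, or that the trial's main conclusion is compromised. The documents support neither. The share returning and its excess risk are not given, and CMDD-M scores discharge documents rather than revisits, so the primary outcome is not directly affected. The reason to act is that the lean has a known direction, the planned adjustment does not address it, and the correction is nearly free.

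**What to change.** Keep the rule and, before the statistical analysis plan is finalised:

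1. Add prior-year emergency department visits and prior-year hospital admissions to the adjusted models for the revisit, readmission, emergency-visit and time-to-event outcomes.
2. Prespecify a sensitivity analysis for those outcomes that applies one look-back to both groups: keep only patients with no study-ward stay in a window before the index admission as long as the span from the start of control enrolment to the end of intervention enrolment (about 14 months as planned, or the actual span if longer). Everyone barred as an earlier control would fail this look-back anyway, so the rule then no longer separates the groups.
3. Report how many intervention-period patients were excluded as already included, and state whether pilot participants counted as such.

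The first change uses data already collected. The second needs ward-specific prior admission dates from the health records, since the protocol lists only a past-year count, and it gives slightly lower precision in that one analysis. The third needs only the screening log. Recruitment does not change.

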### Intervention development

The intervention aims to improve medication communication during the discharge process for older patients. It was designed by a multidisciplinary team comprising researchers with backgrounds in social science, pharmacy, medicine and nursing. Several team members also work professionally as healthcare practitioners in clinical settings, contributing practical insights from ongoing patient care. In addition, the team included two public representatives, ensuring that the perspectives of patients and informal caregivers were meaningfully integrated. The design built on findings from previous research conducted by our group.^12 19 22^ The inclusion rate, as well as the feasibility of selected intervention components and outcome measures, was tested in unpublished pilot studies conducted at geriatric and surgical wards at Uppsala University Hospital, Sweden. These studies involved a total of 106 patients between September 2023 and May 2024 ([name], [name], [name], [name], *et al*: Facilitating patient empowerment at hospital discharge: A pilot study testing the feasibility of the IMPACT-care intervention, unpublished). Based on the results of these pilot studies, the intervention and study design were refined before advancing to the main trial.

### Control period (pre-intervention)

During the control period, care as usual will be provided at the study wards. Clinical pharmacists are part of the care team at the wards and primarily assist with medication reviews at patient admission and discharge but are not routinely involved in the discharge communication process. At hospital admission, medication reconciliation is conducted by either a pharmacist or a physician. If needed, a medication review is carried out by the physician, with or without support from a pharmacist. Any changes to the patients’ medication lists are made by wards physicians or nurse practitioners (specialised nurses at the surgical wards). Oral medication-related communication with the patient and/or informal caregiver is typically handled by nurses, physicians and pharmacists during patient consultations. At discharge, hospitals are required to provide a discharge summary to the next healthcare provider(s) and a discharge letter intended for the patient.^34 35^ Both documents are typically prepared by ward physicians and include details about the hospitalisation, medication changes (along with the rationales for those), planned treatment duration and follow-up plans. The discharge letter, however, is expected to be written in layman’s language. In some cases, these discharge documents are written by a physician who has not met the patient prior to discharge. Pharmacists sporadically assist in preparing these discharge documents, but not in a standardised manner. Additionally, it is standard practice for ward physicians to send specific referrals to the next healthcare provider(s), outlining follow-up requests related to medication changes. In addition, ward physicians conduct an oral discharge consultation, during which the patient is informed about the medication changes and follow-up plans before discharge.

While patients receive written information materials with practical information about the wards and surgical procedures at admission, no materials specifically address medications or medication communication at discharge. Inviting informal caregivers to participate in discharge consultations and HCPs conducting follow-up calls after discharge occurs in selected cases but is not routine practice.

### Implementation period: training of HCPs

The training period will last approximately 2 months between the control and intervention phases. During this period, HCPs—primarily physicians and pharmacists on the study wards—will undergo training. Training of physicians will focus mainly on the importance of writing discharge documentation and effectively using pharmacist support for this process. Training of pharmacists, on the other hand, will focus on implementing the intervention components and understanding the principles of person-centred medication communication at discharge. The training will be delivered through multiple sessions led by the researchers, addressing how the study may impact daily ward processes and how to integrate the intervention components into existing practices. To accommodate newly hired HCPs during the intervention period, as well as those unable to attend the live sessions, digital training materials will be developed and distributed to ensure that all necessary training can be completed. Additionally, the pharmacists, who play a central role in delivering the intervention components, will receive a standardised operation procedure document. Other HCPs on the wards, excluding physicians and pharmacists, will be informed about the study through meetings and information emails, which will outline how they may be affected by the study. For training purposes, selected patients will undergo the intervention components without being included in the study. Additionally, one of the researchers will also regularly visit the study wards to support the HCPs in implementing the intervention components during this phase.

